### 2.12. Study Duration

Based on the hospitals’ discharge frequency, we estimate recruiting patients for six months and collecting data for another six months after reaching the target sample and cluster size; therefore, the study will last one year.

### 2.13. Ethics and Dissemination

The BRAHIT study protocol is approved by Brazil’s National Ethics Committee, with the number 14894819.5.0000.5272. All patient data will be followed up by the research team throughout the study, in addition to usual care, upon municipality authorisation. There will be no interference in the cases’ management apart from the designed actions of the study. During recruitment, we will request consent via a written consent form (Annex) from all physicians and patients involved in the clinical trial. The project is registered in the domain www.clinicaltrials.gov under the number NCT04466852.

## 3. Results

### 3.1. Data Collection Methods

We will collect primary care practices’ data to assess stratification factors (presence of family health strategy exclusively in the practice and population’s socioeconomic status) from Rio’s publicly accessible health system websites [16,34,35,36]. We will obtain a monthly report from the Health Secretariat about hospital admissions containing name, birth date, social identification number (CPF), national health system identification number (CNS), address, hospital, admission date, admission diagnosis, outcome (discharge/transference/death), discharge diagnosis, discharge date, and procedures. Data about the patient’s primary care practice (name, address, phone number, responsible physician) will be collected from the public website *Onde Ser Atendido* [23].

The recruiters will collect baseline data about the physicians through direct inquiry during recruitment. For patient data, we will receive a report extracted from primary care electronic health records including patients’ clinical data, completed during patient recruitment through direct inquiry, to minimise missing data. We will insert data using a REDCap © platform digital form. Baseline collected variables and a description of form fields are summarised in Table 2.

In the intervention group, during teleconsultation, the primary care physician and the teleconsultant (cardiologist) will insert data about the process using a specific form on a digital e-consultation platform designed for the project. The form contains the same fields as the REDCap© form, the reason for teleconsultation, and boxes for text messages. Data from the e-consultation platform will be exported to REDCap© for storage and analysis. In the control group, the recruiter will inform the physician that data from patients with heart failure who were recently discharged from the practice will be collected at baseline and after six months of allocation. We will train all the physicians in using the e-consultation platform.

During recruitment, interviewers assigned to the project will apply paper questionnaires about quality of life (EQ-5D-5L questionnaire) [37,38,39] and heart failure symptoms frequency (Symptom Status Questionnaire—SSQ-HF) [40,41] for baseline assessment.

After six months of the allocation, we will repeat the described data collection for admissions, serious adverse events, and primary care electronic health records and re-apply EQ-5D-5L and SSQ-HF questionnaires. We will collect mortality data from a report on mortality provided by the Health Secretariat.

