## Abstract

Heart failure is a prevalent condition and a frequent cause of hospital readmissions and poor quality of life. Teleconsultation support from cardiologists to primary care physicians managing patients with heart failure may improve care, but the effect on patient-relevant outcomes is unclear. We aim to evaluate whether collaboration through a novel teleconsultation platform in the Brazilian Heart Insufficiency with Telemedicine (BRAHIT) project, tested on a previous feasibility study, can improve patient-relevant outcomes. We will conduct a parallel-group, two-arm, cluster-randomised superiority trial with a 1:1 allocation ratio, with primary care practices from Rio de Janeiro as clusters. Physicians from the intervention group practices will receive teleconsultation support from a cardiologist to assist patients discharged from hospitals after admission for heart failure. In contrast, physicians from the control group practices will perform usual care. We will include 10 patients per each of the 80 enrolled practices (n = 800). The primary outcome will be a composite of mortality and hospital admissions after six months. Secondary outcomes will be adverse events, symptoms frequency, quality of life, and primary care physicians’ compliance with treatment guidelines. We hypothesise that teleconsulting support will improve patient outcomes.

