### 2.4. Interventions

The intervention comprises teleconsultation support from a cardiologist to a primary care physician in reference to the case management of a patient included in the study.

Based on the primary discharge diagnosis, the research team will collect admissions due to decompensated heart failure, from monthly reports provided by the municipality. We will invite the eligible patients and their corresponding primary care physicians to participate in the study. Invitations will be issued by texting, telephone call, or in-person contact, and signed informed consent forms from patients and physicians will be obtained. 

After the patient and physician agree to participate, we will sign up the physician on a secure online platform for teleconsultation hosted on the research team’s web domain. Through a digital form, they will provide data about professional identification, contact information, patient demographics, and clinical data. They will use the practice’s computers or their own devices to connect and discuss the case with the teleconsulting cardiologist.

The consultant cardiologists must be active National Institute of Cardiology staff members and perform academic activities in undergraduate or graduate programs. They are trained in heart failure management and in using the project’s digital tools. They will use the computers from the research department at the National Institute of Cardiology (INC) or personal devices to access the platform at least twice a week on working days and give feedback to primary care physicians about clinical management. 

The interactions may happen asynchronously, via the teleconsultation platform’s message interface or WhatsApp© texting, or synchronously, by phone call or videoconference, at the physicians’ preference. The duration of the teleconsultation period will depend on the physician’s judgment. This approach is designed to ensure the pragmatism of the intervention [21,22]. Besides the changes recommended by the teleconsultation, all patients will receive the usual care planned by their practice teams, including physician and nurse consultations, prevention measures, oral health treatment, and community agent follow-up visits.

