## Figures and Tables

**Figure 1 ijerph-20-05933-f001:**
[figure not shown]
Study workflow.

**Table 1 ijerph-20-05933-t001:** Participant Timeline.

Enrolment	T_−1_	T_0_	T_6_ (Close-Out)
General practice stratification and randomisation	X		
Patient eligibility screening using municipality data	X		
Invitation to participate (patient)	X		
Invitation to participate (physician)	X		
Informed consent (patient and physician)	X		
Patient allocation according to practice randomisation		X	
Intervention			
Intervention group		Teleconsultation support for the practice’s physicians (first contact and on demand)	
Control group		Usual care with follow-up of outcomes	
Assessments		T_0_	T_6_ (close-out)
1—Readmissions and Mortality (reports)			X
2—Days Alive Out of Hospital (DAOH)			X
3—Frequency of Serious Adverse Events			X
4—Symptoms Frequency and Severity		X	X
5—Quality of Life		X	X
6—Adherence to Prescribing Guidelines		X	X

**Table 2 ijerph-20-05933-t002:** Baseline Variables.

N	Variable	Field Type	Choices, Calculations, or Labels
Physician Variables—direct inquiry			
1	Name	Text	-
2	Social Identification Number (CPF)	Text	-
2	Completed years since graduation	Number	-
3	Specialisation	Option	Any/Family Medicine/Other
4	Completed years in primary care	Number	-
5	Completed years in the current practice	Number	-
6	Enrolled in a residency program	Options	No/Preceptor/1st year Resident/2nd year Resident/3rd year Resident/Program
Patient Variables—primary care electronic health record report			
1	Name	Text	-
2	Social identification number (CPF)	Text	-
3	National Health System identification number (CNS)	Text	-
4	Primary care practice	Text	
5	Gender	Options	Feminine/Masculine/Nonbinary
6	Race	Options	White/Black/Brown/Other
7	Birth date	Date	-
8	Weight (Kg)	Number	-
9	Height (cm)	Number	-
10	NYHA status	Options	1 to 4
11	Systolic blood pressure	Number	-
12	Diastolic blood pressure	Number	-
13	Heart rate	Number	-
14	Dyspnoea	Option	Yes/No
15	Leg Swelling	Option	Yes/No
16	Dizziness	Option	Yes/No
17	Fatigue	Option	Yes/No
18	Orthopnoea or paroxysmal nocturnal dyspnoea	Option	Yes/No
19	Syncope	Option	Yes/No
20	Typical chest pain	Option	Yes/No
21	Jugular vein distension	Option	Yes/No
22	Pulmonary rales	Option	Yes/No
23	ACE-I (names)	Option	ACE-I names
24	ACE-I dose	Number	-
25	ARB (names)	Option	ARB names
26	ARB dose	Number	-
27	Beta-blockers (names)	Option	BB Names
28	Beta-blockers dose	Number	-
29	Spironolactone	Option	Yes/No
30	Spironolactone dose	Number	-

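### Platform training is promised to all physicians, not only those in intervention practices, which puts the usual-care contrast at avoidable risk for no stated reason

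*Protocol article*

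**What the plan says.** The training sentence is in section 3.1 (Data Collection Methods) of the protocol article: "We will train all the physicians in using the e-consultation platform". It carries no restriction by arm and comes immediately after the sentence on the control group, which begins "In the control group, the recruiter will inform the physician that data from patients with heart failure".

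The control condition is stated twice. The Abstract says that "physicians from the control group practices will perform usual care", and Table 1 gives the control arm "Usual care with follow-up of outcomes".

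The only use of the platform that section 3.1 describes belongs to the other arm: "In the intervention group, during teleconsultation, the primary care physician and the teleconsultant (cardiologist) will insert data about the process". Clinical data at patient level have a separate source: "For patient data, we will receive a report extracted from primary care electronic health records". These data are completed by direct inquiry at recruitment and entered in REDCap.

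Section 2.4 (Interventions) defines what is being tested: "The intervention comprises teleconsultation support from a cardiologist to a primary care physician". The same section says that, after patient and physician agree to take part, "we will sign up the physician on a secure online platform for teleconsultation".

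**The concern.** A usual-care arm is informative only if it stays close to usual care. Training control physicians on the tool that delivers the intervention brings them nearer to it, and the article names nothing that this achieves.

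Two routes to dilution are conceivable; both are inferences, not statements in the article. First, a trained control physician knows that the service exists and how it is used, and no sentence expressly bars access before six months. Second, the platform form has the same fields as the REDCap form. If those include the clinical variables of Table 2, they cover NYHA class, vital signs, and use and dose of ACE inhibitors, ARBs, beta-blockers and spironolactone. Table A1 scores the same drug classes for the exploratory adherence outcome, so going through the form could prompt some of the prescribing that is later measured.

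Any such effect would move the control arm towards the intervention arm, shrink the difference in the primary outcome and lower power.

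**Working it through.** **Step 1: the text.** Three questions decide whether the sentence fits the design.

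- *Whom does it cover?* All physicians, stated straight after the control-group sentence. The plain reading includes controls.
- *Do controls need the platform?* None of the places cited gives them a task on it. Their patients' data come from record reports and direct inquiry, and the physician is only told that data will be collected.
- *Do controls get the intervention?* No passage says so. The intervention is the cardiologist's support, and the article describes its delivery only for the intervention group.

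The training sentence is therefore out of line with the control condition, but it does not itself deliver the intervention to controls.

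**Step 2: reproduce the plan's sample size.** Inputs from section 2.11.1: control rate 40.1%, effect 30%, ICC 0.05, 10 patients per cluster, 5% type I error, 80% power. Two-sided testing is assumed. Read as relative, the effect gives p2 = 0.401 × 0.70 = 0.2807, so Δ = 0.1203.

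- n per arm = [1.96√(2p̄q̄) + 0.8416√(p1q1 + p2q2)]² / Δ², with p̄ = 0.34085
- = (1.3138 + 0.5596)² / 0.01447 = 242.5, rounded up to 243
- Design effect = 1 + 9 × 0.05 = 1.45; 243 × 1.45 = 352.35, rounded up to 353 per arm
- 353 / 10, rounded up, is 36 practices per arm, or **72 in total**, as stated

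**Step 3: illustrate dilution at the planned 80 practices.** Effective size per arm is 400 / 1.45 = 275.9, with square root 16.61. If a share c of the effect reaches controls, the control rate falls to 0.401 − 0.1203c and the intervention rate stays at 0.2807.

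Power = Φ{[Δ × 16.61 − 1.96√(2p̄q̄)] / √(p1q1 + p2q2)}

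- c = 0: (1.9981 − 1.3138) / 0.6649 = 1.029, power 84.8%
- c = 10%: (1.7983 − 1.3081) / 0.6630 = 0.739, power 77.0%

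| Share reaching controls (assumed) | Control rate | Difference (points) | Power, 80 practices | Practices for 80% power |
|---|---|---|---|---|
| 0% | 40.1% | 12.0 | 84.8% | 72 |
| 5% | 39.5% | 11.4 | 81.2% | 78 |
| 10% | 38.9% | 10.8 | 77.0% | 88 |
| 20% | 37.7% | 9.6 | 67.3% | 110 |

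**Step 4: sensitivity.** Section 2.11.1 also speaks of a 15% difference. Taken as 15 absolute points (40.1% versus 25.1%), it requires 46 practices, not 72. With 80 practices, power is then 96.6%, 95.0%, 92.8% and 86.3% for the same four shares. The loss of power thus depends on which effect is meant. The 40.1% is also an annual rate while the outcome is read at six months, so neither set of figures is a forecast.

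**The case against.** The strongest reply is that training on a tool is not the intervention. Contamination through the service needs a cardiologist to answer about a control patient, and nothing offers that to controls. Section 2.13 promises no interference in case management beyond the study's own actions, and section 2.9 assigns a researcher to monitor the teleconsulting process. This stands, and it is why the point is put as a risk of unknown size.

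Four stronger readings are tempting, and the article does not support them.

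- *Controls receive accounts.* A reader might infer this from the sign-up sentence in section 2.4, which names no arm. But it stands under Interventions, in a paragraph about physicians who go on to discuss the case with the cardiologist. In context it describes the intervention arm.
- *Training has no benefit.* No purpose is stated, which does not prove that there is none. The sentence is in the data-collection section, the form shares its fields with REDCap, and a condensed article may omit the reason. Data capture or equal contact in both arms is possible.
- *Training reveals the arm.* If everyone is trained, training cannot distinguish the arms.
- *Power will fall by the amounts in the table.* No contamination rate is given, and nothing links platform training to any particular share.

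It can also be said that the sentence loosely means all physicians who will use the platform. That is possible, but staff who follow it as written would train controls, so the wording still needs correcting.

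**Conclusion.** The point holds as a poorly scoped rule that carries an avoidable risk. As written, the protocol trains control physicians on the intervention's tool, while the article gives them usual care, no platform task and no stated reason for training. Whether this would change their care, and by how much, cannot be determined from the document.

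On the effect that reproduces the stated 72 practices, the planned 80 keep power above 80% at 5% dilution (81.2%) but not at 10% (77.0%). This rests on assumed dilution rates, a two-sided test, an ICC of 0.05 and an annual event rate. If a 15-point difference is meant, power stays above 80% even at 20% dilution. The case for change therefore rests on the mismatch in the text and the low cost of removing it, not on a demonstrated loss of power.

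**What to change.** Reword the training sentence in section 3.1 so that platform training and accounts are limited to physicians in intervention practices and given after allocation. Control physicians should receive only the information on data collection. Platform training can be offered to control practices after their last six-month assessment. Adding to section 2.4 that sign-up applies to the intervention arm would remove the remaining ambiguity.

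If control physicians must be trained for data capture, the protocol should say so and state that they have no teleconsultation access before the six-month outcome.

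The cost is a sentence or two of text and less training work during the trial. The downside is that training contact then differs between arms. This is minor, because section 2.8 already accepts that care providers cannot be blinded.

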### 3.2. Outcomes

The primary outcome will be a composite of all-cause mortality or one or more hospital readmissions. Any pre-hospital or hospital stay because of heart failure will be considered as a readmission [42,43]. Secondary outcomes will include hospital-free days within 180 days [44,45,46], serious adverse events (defined as any adverse event that results in death, is life-threatening, requires hospitalisation or prolongation of existing hospitalisation, or results in persistent or significant disability or incapacity, measured in municipality admission reports), frequency and intensity of heart failure signs and symptoms, measured using the Symptom Status Questionnaire—Heart Failure—Brazilian Version (Appendix A) [40,41], computed as a 0 to 84 score, and health-related quality of life, measured using the EQ-5D-5L questionnaire [37,38] scored using a value set validated for the Portuguese version [39] on a visual-analogic scale (0 to 100).

An exploratory outcome will be physicians’ adherence to guidelines, comparing prescription data to guidelines and quality standards using a compliance score (Table A1 in Appendix B) [47,48,49,50]. We will measure all outcomes at the patient level, at baseline when meaningful, and after six months of allocation.

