### 2.6. Recruitment (Patient and Provider)

A recruitment researcher (recruiter) will receive once monthly a database of admissions from the municipality Health Secretariat, including patients with a registered heart failure ICD-10 code (I11.0, I13.0, I42.0, I42. 6, I42.9, I50. 0, I50.1 or I50.9) who have been discharged during the previous month. Within one week, they will identify the primary care practice where the patient is registered, according to the patient’s address, in the public database *“Onde Ser Atendido”* [23] and invite the correspondent physician, who is responsible for the care of the patient, to participate in the study, by e-mail, telephone, or in person at the practice. When the physician accepts, the recruiter invites the patient by telephone or in person. We expect to invite all discharged patients from the municipality database (an average of 127 patients per month) and a 10% refusal rate, with an estimated recruitment rate of 114 patients/month, lasting for eight months, from March to September 2023. The recruitment will stop once the target sample size of 80 clusters with 10 patients each is reached.

The recruiter will obtain consent forms from patients and physicians, deliver orientation about the study process, and monitor the recruitment rate weekly. No financial incentive will be provided for the enrolment either of patients or physicians.

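### The protocol does not say that the admission extract used for serious adverse events is all-cause, and the pooled definition lets a heart failure benefit offset other harm

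*Protocol article*

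**What the plan says.** Section 3.2 of the protocol article makes serious adverse events a secondary outcome. The definition covers any adverse event that is fatal or life-threatening, or that "requires hospitalisation or prolongation of existing hospitalisation, or results in persistent or significant disability or incapacity, measured in municipality admission reports". No other source is named for this outcome in that section.

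The municipality report appears in three places:

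- Section 2.4: "the research team will collect admissions due to decompensated heart failure, from monthly reports provided by the municipality", selected on the primary discharge diagnosis.
- Section 2.6: the recruiter receives a monthly database of admissions, "including patients with a registered heart failure ICD-10 code" from a list of eight codes. Its size is also given: "We expect to invite all discharged patients from the municipality database (an average of 127 patients per month".
- Section 3.1: "We will obtain a monthly report from the Health Secretariat about hospital admissions containing name, birth date" and other identifiers, and ending with "outcome (discharge/transference/death), discharge diagnosis, discharge date, and procedures". No diagnosis limit is mentioned.

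For follow-up, section 3.1 says that six months after allocation "we will repeat the described data collection for admissions, serious adverse events" and health records. Deaths come from a separate mortality report.

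The primary outcome (section 3.2) is death from any cause or at least one readmission, where a readmission is a hospital or pre-hospital stay because of heart failure. Hospital-free days within 180 days are another secondary outcome, with no source stated.

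**The concern.** Serious adverse events are the trial's dedicated harm outcome, and the Discussion presents the study as addressing safety as well as effectiveness. The harm outcome therefore needs to register hospitalisations that the primary outcome does not count, that is, those for reasons other than heart failure. Two features put this at risk.

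First, the protocol describes one monthly municipality report, gives it a heart failure code list where recruitment is described, and then refers back to the described collection at six months. If the same feed is reused, an enrolled patient admitted for another reason and discharged alive leaves no record. Hospital-free days would be overstated in the same way if they were taken from that feed.

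Second, whatever the extract, the pooled definition contains the primary outcome's deaths and heart failure hospitalisations. If the intervention reduces these, the total falls, and a rise in other serious events can disappear inside it.

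**Working it through.** **Step 1. Which report is it?** The plan gives no figure for serious adverse events, so this step compares the text.

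- Pointing to the filtered feed: section 2.7.3 uses the monthly Health Secretariat report to allocate patients, section 2.6 describes the monthly database by heart failure codes, and the fields in section 3.1 include the address, which section 2.6 uses to find the practice. The list averages 127 discharged patients a month. Section 2.2 expects about 15,378 admissions a year among people with heart failure in the city, or 15,378 / 12 = about 1,282 a month. A list of 127 is not an all-cause list for the city.
- Pointing to a wider report: section 2.4 has the research team pick out heart failure admissions, section 3.1 states no diagnosis limit, and the six-month sentence stands in section 3.1 and lists serious adverse events separately from admissions.

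Reuse of the recruitment feed is the more natural reading, but no sentence settles it.

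**Step 2. If the feed is filtered.** Captured events are heart failure stays, plus deaths from the mortality report. These are the event types of the primary outcome. Non-fatal hospitalisations under other codes are not recorded.

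**Step 3. If the extract is all-cause, how large can the offset be?**

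Inputs from section 2.11.1: a composite of 40.1% per year and a 30% effect. That 30% is relative can be checked: 40.1% against 0.7 × 40.1% = 28.1% needs 243 per arm at 5% two-sided error and 80% power; 243 × (1 + 9 × 0.05) = 352.35, which is 36 clusters of 10 per arm, the stated 72 in total.

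Assumptions, not in the document: constant hazard over the year; other serious events independent of the composite; control risk of other events 10%, 20% or 30%; every primary event counts as a serious adverse event.

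- Six-month composite, control: 1 − (1 − 0.401)^0.5 = 22.6%.
- Intervention: 0.7 × 22.6% = 15.8%.
- Pooled risk = 1 − (1 − composite)(1 − other).
- Other events rising from 10% to 15%: control 1 − 0.774 × 0.90 = 30.3%; intervention 1 − 0.8418 × 0.85 = 28.4%.

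Other events rise by half, yet the pooled risk is lower in the intervention arm.

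Break-even: the intervention risk of other events at which the pooled risks are equal is 1 − 0.774 × (1 − control risk) / 0.8418.

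| Control risk, other events | Break-even intervention risk | Ratio |
|---|---|---|
| 10% | 17.3% | 1.73 |
| 20% | 26.4% | 1.32 |
| 30% | 35.6% | 1.19 |

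If 40.1% is applied at six months without conversion, the 10% to 15% example gives 1 − 0.599 × 0.90 = 46.1% against 1 − 0.7193 × 0.85 = 38.9%, a larger offset. If the intervention has no effect on the composite, there is no offset.

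**The case against.** The strongest reply is that the code list belongs to recruitment. It is stated only in section 2.6, for finding eligible patients, and the 127 a month sizes the pool to invite, not the follow-up query. Section 3.1 describes a report about hospital admissions without a diagnosis limit, and section 2.4 has the team do the selecting. This stands. A reader might infer that the safety outcome cannot capture any harm outside heart failure and simply becomes the primary outcome under another name. The document does not support that: the filter is never stated for the outcome extract, and deaths from any cause come from the mortality report in any case.

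A reader might likewise infer that hospital-free days are certainly wrong. No source is stated for them, so that too is conditional.

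The reply also notes that an all-cause definition always overlaps a primary outcome of death or hospitalisation, that tabulation by cause is usually left to the analysis plan, and that the discharge diagnosis needed for a split is already collected. That is fair, and the missing table alone would be no finding. But the protocol itself fixes both the definition and the source, and the scope of the data request decides whether a useful split will be possible.

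Finally, section 2.11.2 rests the main conclusions on the primary outcome and treats secondary outcomes as hypothesis-generating. Mortality, symptoms and quality of life can also show worsening. This lowers the severity but does not remove the point.

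**Conclusion.** The concern holds as an open question of scope with a real consequence, and as a weakness of the pooled count. The protocol ties serious adverse events to the municipality admission reports, describes one such report with a heart failure code list at recruitment, and never says that the outcome extract is all-cause. If the recruitment feed is reused, non-fatal admissions for other causes are lost; how many cannot be estimated from the document. If the extract is all-cause, those admissions are recorded, but the pooled total can still mask a rise in them of up to 1.73-fold, 1.32-fold or 1.19-fold at control risks of 10%, 20% or 30%. These ratios apply to the unfiltered case only and rest on the assumptions above, including that the intervention achieves its planned effect. A code filter on heart failure would not by design remove primary outcome events, so the main conclusion is not at stake. This is a cheap improvement of moderate severity.

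**What to change.** 1. State in sections 3.1 and 3.2 that the outcome extract covers all admissions and pre-hospital stays of enrolled patients from allocation to day 180, whatever the ICD-10 code, linked on CPF/CNS. Keep the code list for recruitment only.
2. Name this extract as the source for serious adverse events and for hospital-free days.
3. Report serious adverse events by arm in total and split, using the discharge diagnosis, into those that are also primary-outcome events and all others.

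The cost is a wider query to the same data provider for about 800 patients whose identifiers are already held, and one more table. The non-primary part has fewer events than the total, so its relative risk will have a wider interval.

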### 2.10. Data Management

The research team has a secure REDCap© environment hosted at the National Institute of Cardiology of Brazil server, where databases and forms will be created and hosted, comprising data from primary care practices and physicians collected from public websites, randomisation lists, reports shared by the municipality about hospital admissions, primary care clinical data, mortality data, recruitment assignments and monitoring, and the answers to patient-reported outcomes questionnaires. A database and a reporting system have been developed within the e-consultation platform for management of intervention data, hosted at a secure web domain contracted by the project team. 

Researchers will only have access permission to data concerning their specific activities (e.g., recruiter, teleconsultant, data analyst) on REDCap© and the e-consultation platforms. Access will be granted through individual passwords changed regularly. The data manager will perform a weekly scheduled backup to a different server. 

For analysis, all data will be merged into one single database on the study’s REDCap© environment, based on the patients’ single identifier numbers (CPF). The data management team will monitor missing data and apply measures to communicate and minimise any lack. We will store the complete database for one year after the end of the study and share anonymised datasets in a dataset repository. 

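### The serious adverse event outcome is defined to include death, life-threatening events and disability, but its one named source, the admission report, shows only events tied to a recorded stay

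*Protocol article*

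**What the plan says.** Section 3.2 (Outcomes) lists serious adverse events among the secondary outcomes, "defined as any adverse event that results in death, is life-threatening, requires hospitalisation or prolongation of existing hospitalisation", and closes the definition with events where the outcome "results in persistent or significant disability or incapacity, measured in municipality admission reports". That closing phrase, "measured in municipality admission reports", gives the only source the article names for this outcome.

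Section 3.1 (Data Collection Methods) lists the contents of the monthly admission report. Apart from identifiers, address and hospital, these are "admission date, admission diagnosis, outcome (discharge/transference/death), discharge diagnosis, discharge date, and procedures". At six months, "we will repeat the described data collection for admissions, serious adverse events, and primary care electronic health records". A separate sentence then adds: "We will collect mortality data from a report on mortality provided by the Health Secretariat". Nothing ties that mortality report to the serious adverse event outcome. Table 1 also has one row for readmissions and mortality from reports and another for the frequency of serious adverse events.

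Deaths matter elsewhere in the plan too: "The primary outcome will be a composite of all-cause mortality or one or more hospital readmissions". Under section 2.10, "all data will be merged into one single database on the study’s REDCap© environment, based on the patients’ single identifier numbers (CPF").

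**The concern.** The article defines an outcome and then fixes a source that cannot deliver all of it. This is different from a procedure left to a fuller document, because the source is stated.

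This is the only outcome listed as a harm, and the Discussion says the trial addresses a knowledge gap on safety as well as effectiveness. If the stated source is followed, the count covers recorded stays and deaths during them. A patient who dies at home has a serious adverse event by the article's definition and none by its measurement. A reader of the results table would take the row at its definition and not know that some fatal events had been left out.

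**Working it through.** **Step 1. Each part of the definition against the named source.** The definition is in section 3.2, the report fields in section 3.1.

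| Part of the definition | Visible in the admission report? | Other source described? |
|---|---|---|
| Death during a recorded stay | Yes, through the outcome field | Mortality report |
| Death outside hospital | No | Mortality report, but not assigned to this outcome |
| Life-threatening event with admission | Yes, because the admission itself qualifies | Not needed |
| Life-threatening event without admission | No | None assigned |
| Hospitalisation | Yes | Not needed |
| Prolongation of a stay | Only indirectly, from the dates | None assigned |
| Persistent or significant disability | No field for it | None assigned |

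The six-month sentence in section 3.1 does not close the gap. It repeats the collection already described, and no separate collection of serious adverse events is described before it.

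**Step 2. Where the missing deaths go.** Deaths outside hospital are in the mortality report, which is merged with the other data by patient identifier (section 2.10). They enter the primary composite through all-cause mortality. They should also affect hospital-free days, which Table 1 labels as days alive out of hospital. So they are absent from one secondary tally and not from the trial.

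**Step 3. Scale.** The article gives no figure for this outcome, so only an illustration is possible.

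Inputs: annual mortality 24% (section 2.2); planned sample 80 × 10 = 800 (Abstract).

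Check of the input: 63,204 × 0.249 × 0.24 = 3,777, which is the number of deaths printed in section 2.2. The 24% was therefore applied to admitted patients.

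Six-month mortality:
- Linear: 0.24 × 0.5 = 0.120, and 0.120 × 800 = 96 deaths.
- Constant hazard: 1 − 0.76^0.5 = 0.128, and 0.1282 × 800 = 102.6, about 103 deaths.

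The share of deaths outside hospital is not in the article. The shares below are assumptions:

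| Assumed share outside hospital | Linear (96 deaths) | Constant hazard (102.6 deaths) |
|---|---|---|
| 10% | 9.6 | 10.3 |
| 20% | 19.2 | 20.5 |
| 30% | 28.8 | 30.8 |
| 50% | 48.0 | 51.3 |

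The range is about 10 to 51 fatal events missing from the serious adverse event count, both arms together. Two things limit even this illustration. Section 2.2 does not say whether its 24% includes deaths during the index stay, while section 2.3.1 enrols only discharged patients, so 96 to 103 may be too high. And no split by arm can be derived.

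**The case against.** The strongest reply is that nothing is lost that matters for the conclusions. The mortality report is obtained, the data are linked, all-cause mortality is in the primary outcome, and section 2.11.2 rests the main conclusions on that outcome and treats secondary results as hypothesis-generating only. Section 3.2 does not say that admission reports are the only source, and a condensed article may leave safety procedures to a fuller document. Section 2.8 mentions a data safety monitoring committee whose procedures are not shown.

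Most of this stands, and it limits the point to one secondary outcome. It does not remove the mismatch. The article chose to state a source, that source does not fit the definition, and no other is assigned to the outcome. The composite is also not a full substitute: it registers each patient once, so a death at home after a readmission adds nothing to it.

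Three stronger readings are tempting, and the documents do not support them:
- A reader might infer that out-of-hospital deaths are hidden from the trial and that safety would be falsely reassured. They are collected and counted in the primary composite.
- A reader might call this the main safety outcome. The article does not. It is one of several secondary outcomes, though the only one listed as a harm.
- A reader might infer that using the admission report is what makes the count fall when admissions fall. Hospitalisation is itself a qualifying criterion, so the count would fall with admissions whatever the source. Adding the mortality report does not remove that dependence. Reporting fatal and non-fatal events separately makes it visible.

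**Conclusion.** The point holds as a mismatch between definition and source. As written, the serious adverse event count would omit deaths outside hospital, and it has no described way to detect disability or life-threatening events without an admission.

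The number omitted cannot be computed from the documents. The figure of about 10 to 51 fatal events rests on the article's 24% annual mortality, on 800 patients followed for six months, and on an out-of-hospital share of 10% to 50% that is purely assumed. It describes what is absent from this tally. It is not an estimate of data lost to the trial, and it says nothing about the size or direction of any difference between arms.

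The defect is worth correcting before analysis, but it does not threaten the primary comparison.

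**What to change.** In section 3.2:

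1. Name the municipality admission report and the Health Secretariat mortality report together as the sources for serious adverse events.
2. Count every death within 180 days of allocation as a serious adverse event, wherever it occurred. Section 3.2 already uses 180 days for hospital-free days.
3. Report fatal and non-fatal events separately by arm, so that a change in admissions cannot mask a change in deaths.
4. Restrict the remaining parts of this outcome's definition to what the two reports can show, and say so. On the fields listed, that leaves out disability and life-threatening events without an admission.

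The cost is a sentence or two and one more row in the results table. Both reports are already being obtained and the merge by patient identifier is already planned, so no new data collection is needed.
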